### Laboratory Analysis

Saliva and blood samples were processed according to standard procedures and stored at –20 °C until analysis by ELISA to identify SARS-CoV-2–reactive antibodies. A previously established and validated in-house ELISA to detect antibodies against SARS-CoV-2 in saliva was performed [20]. Blood samples from the validation group cohort will be analyzed using a certified commercial ELISA by EUROIMMUN to quantify immunoglobulin G reactive to the S1 domain of the of SARS-CoV-2 spike protein.

### Data Management

The case report form is the source document for all personal data. Each participant included in the study received a unique identifier. All data were collected on paper forms and were entered and pseudonymized into an electronic database.

### Data Analyses

Data will be typed into Excel (version 16.51; Microsoft), and graphics will be generated with Prism (version 9.1; GraphPad) and RStudio (version 1.2.5001) running R (version 4.0.4; The R Foundation). Simple descriptive statistical analyses will be conducted. Depending on the classification of the data, parametric or nonparametric tests will be used. Correlation and regression models will be analyzed using RStudio. The estimated prevalence will be computed and adjusted using the R package epiR (version 0.9-43).

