### Study Population

Children and adolescents were enrolled and sampled via preschools, primary schools, and secondary schools randomly spread over the Tübingen city area. In total, 1850 children and adolescents were enrolled: (1) preschools—infants aged 1 to 3 years (n=350) and young children aged 4 to 6 years (n=350), (1) primary schools—children aged 7 to 10 years (n=350), and (3) secondary schools—children and adolescents aged 11 to 18 years (n=800). Study participants and their families were informed about the study and its aims via their institutions. In addition to all relevant documents, families were also provided with a link to a video that explains the study (Multimedia Appendix 1) and procedures in an easy-to-understand way to ensure broad participation. Saliva was sampled after written informed consent has been given by parents or legal representatives. Assent from children aged 12 years and older was collected on the day of first sampling. Inclusion criteria include the following: aged 1 to 18 years, enrolled in an educational institution within the city of Tübingen, and written informed consent given or written assent given if the child is 12 years or older. Exclusion criteria include not attending a preschool or school in the city of Tübingen.

For the adult comparator group (n=400), any person aged 18 years and older living or working in Tübingen who had given written informed consent could be enrolled. For the adult validation group (n=40), the following individuals can participate in the study: those with a previous SARS-CoV-2 infection, confirmed by either quantitative polymerase chain reaction or by ELISA with a SARS-CoV-2–specific antibody at any time period before enrollment, who have given written informed consent. Blood and saliva samples are being collected every 2 months for 12 months (Figure 1).

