### Sample Size

Tübingen has a total of 91,656 inhabitants; among them, 4910 are children under the age of 6 years and 8366 are children between the ages of 6 and 18 years (≤6 years: n=4061; 7-18 years: n=6621, as of December 31, 2019). Therefore, in total, 13,276 children were living in Tübingen at the time of the study; of these, we aimed to recruit 1850 children and young adults. In addition, 400 adults will be included as an adult comparator group. At the time of planning, 567 out of 100,000 inhabitants—as determined by the Robert Koch Institute in Berlin, Germany, on June 1, 2020—have had a confirmed SARS-CoV-2 infection in the county of Tübingen, but the number of unreported and asymptomatic infections is believed to be higher. Therefore, we expect to have at least 2.2 positive cases in the adult group; in the event that children are infected at an equal frequency, we expect to find at least 10.4 positive cases in children at T1.

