## Discussion

The world was confronted with the COVID-19 pandemic, which has become the biggest public health crisis of recent times, has caused a large number of deaths, and has become a burden on intensive care facilities [2]. The majority of affected persons are older than 18 years, although adolescents and children can also become infected, with recent estimates in the range of 5% [21-23]. Different study designs can provide information on the transmission dynamics in children. Large population-wide serosurveillance studies have been performed in Europe using blood samples [11,24,25]; however, in order to facilitate large population studies in school-aged children, especially if multiple samples are collected from within the same population, saliva samples should be considered. With these factors in mind, the Coro-Buddy study was developed as a prospective, longitudinal study and will report the prevalence of SARS-CoV-2 infection in children in a sample that is representative of the study area, Tübingen, a university city in the south of Germany. The study will also be able to report on the prevalence of previous SARS-CoV-2 exposure in the different age cohorts—1 to 6 years, 7 to 10 years, and 11 to 18 years—as well as the incidence of new cases at three different time points, representing the end of school closures in Germany in summer 2020, and before and after the winter 2020-2021 period.

Children were enrolled and sampled at their respective preschools or school centers to ensure representativeness of the young population in the study area. The infection rate will be determined by measuring antibodies against SARS-CoV-2 in saliva via noninvasive sampling. This approach is particularly amenable for community studies where the significance of the outcome increases by unbiased sampling. The study will also report on a validated saliva-based SARS-CoV-2–antibody ELISA procedure that can be used in future antibody prevalence studies. In addition, the study will report on the number of SARS-CoV-2 infections per institution; this data could contribute to comparative analysis with data collected beyond this study to better understand the pandemic retrospectively.

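### Children are recruited through preschools and schools, but the stated prevalence analysis makes no allowance for clustering of infection by institution

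*Protocol article*

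**What the plan says.** On recruitment, the protocol article (Study Population) says: "Children and adolescents were enrolled and sampled via preschools, primary schools, and secondary schools randomly spread over the Tübingen city area". The age bands are tied to the setting: 1 to 3 and 4 to 6 years in preschools (350 each), 7 to 10 years in primary schools (350), and 11 to 18 years in secondary schools (800). Within an institution, participation was by individual consent: "Saliva was sampled after written informed consent has been given by parents or legal representatives".

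On analysis, Data Analyses says "Simple descriptive statistical analyses will be conducted". It adds that the choice between parametric and nonparametric tests depends on the type of data, that correlation and regression models will be run, and "The estimated prevalence will be computed and adjusted using the R package epiR (version 0.9-43". It does not say what the prevalence is adjusted for.

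The Discussion offers sampling at institutions as the reason the sample is representative. It promises prevalence for ages 1 to 6, 7 to 10 and 11 to 18, and says "the study will report on the number of SARS-CoV-2 infections per institution". Study Design states that each participant is sampled at T1, T2 and T3.

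**The concern.** The virus passes from person to person through the air, as the Introduction says. Children who share a preschool or school share exposure, so a positive correlation of antibody status within institutions is the natural expectation. In that case 1850 children recruited through institutions carry less information about city-wide prevalence than 1850 children drawn independently.

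Prevalence is the study's main objective, so its interval matters. Contrasts between age bands are more exposed still. The three bands in the Discussion coincide with preschool, primary and secondary school, so a comparison of ages is also a comparison of separate sets of institutions, and all variation between institutions falls on it. The expected counts at T1 are very small. Three or four linked infections in one school could look like an age effect in a test that ignores institution.

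**Working it through.** **1. The plan's own figures.** Sample Size gives the planning rate ("At the time of planning, 567 out of 100,000 inhabitants"), 1850 children and 400 adults. Expected positives are n × 567/100,000:
- Children: 1850 × 0.00567 = 10.49 (stated 10.4).
- Adults: 400 × 0.00567 = 2.27 (stated 2.2).

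Both reproduce, apparently truncated. Clustering does not alter expected counts. The section sets no power or precision target, so there is nothing further to reproduce.

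By reported age band, the 10.49 splits as follows:
- 1 to 6 years: 700 × 0.00567 = 3.97.
- 7 to 10 years: 350 × 0.00567 = 1.98.
- 11 to 18 years: 800 × 0.00567 = 4.54.

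**2. Effect of clustering on a single-round prevalence.** Assumed, because the article gives neither: 20, 40 or 80 institutions of equal size, and an ICC of 0.001 to 0.05.
- Mean cluster size: m = 1850/k.
- Design effect: DE = 1 + (m − 1) × ICC.
- Effective sample size: 1850/DE.
- Width factor: √DE.
- Coverage of an interval that ignores clustering: 2Φ(1.96/√DE) − 1. This is a large-sample approximation, so it is rough with about ten positives.
- Intervals shown: Wilson 95% at 0.567%, with n replaced by 1850/DE.

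| Institutions (m) | ICC | DE | Effective n | Width factor | Wilson 95% interval | Coverage if ignored |
|---|---|---|---|---|---|---|
| Independence | 0 | 1 | 1850 | 1 | 0.31–1.03% | 95% |
| 80 (23.1) | 0.001 | 1.02 | 1810 | 1.01 | 0.31–1.03% | 94.8% |
| 40 (46.2) | 0.01 | 1.45 | 1274 | 1.21 | 0.28–1.15% | 89.6% |
| 40 (46.2) | 0.02 | 1.91 | 971 | 1.38 | 0.25–1.27% | about 84.5% |
| 20 (92.5) | 0.05 | 5.58 | 332 | 2.36 | 0.15–2.12% | 59% |

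For example, with 40 institutions and an ICC of 0.02: 1 + (46.25 − 1) × 0.02 = 1.905, and √1.905 = 1.38.

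**3. Effect of repeated measurement.** Each child gives one result per round, so repetition does not touch a single-round interval. For change from T1 to T3, the variance is (v1 + v2 − 2ρ√(v1·v2))/n. Take p1 = 0.567% and, purely for illustration, p2 = 5% (a figure of that order appears in the Discussion), with n = 1850:
- v1 = 0.00567 × 0.99433 = 0.00564 and v2 = 0.05 × 0.95 = 0.0475.
- ρ = 0 (pairing ignored): half-width 1.05 percentage points.
- ρ = 0.3: 0.95 points.
- All T1 positives still positive at T3 (ρ = 0.33): 0.94 points.

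Ignoring a positive within-child correlation therefore makes the interval for change too wide. Only pooling the three rounds as separate records would make an interval too narrow (at ρ = 0.3, DE = 1 + 2 × 0.3 = 1.6), and the article plans no such pooling.

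**The case against.** The strongest objection is that the article never says observations are treated as independent. It names no interval method, leaves the adjustment of the prevalence undefined, and mentions regression models that could include institution. It is a condensed account, and the full protocol or a statistical analysis plan may deal with clustering. This stands in part: independence is what the listed methods imply, not something the article declares. It does not remove the point. The article goes beyond silence: it commits to a set of methods and to a rule for choosing tests that looks at the type of data and not at how the children were sampled. Those methods do not match the sampling it describes, and a specific better method is available.

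Several stronger readings are tempting, but the text does not support them:
- A reader might infer that whole institutions were sampled. The article says only that children were reached through institutions, with individual consent. Clustering does not require a census of each school.
- A reader might infer a binomial interval or independent-sample tests between rounds. Neither is named, and paired tests are not excluded.
- A reader might infer that testing the same children three times also makes intervals too narrow. For the change between rounds the direction is the opposite, and single-round intervals are unaffected.

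The size is also open to challenge. The cluster numbers and ICCs are assumptions, and at the low end the effect is negligible. The two preschool age bands may share institutions, so the argument about nesting applies to the three bands of the Discussion and not to 1 to 3 against 4 to 6 years.

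**Conclusion.** The point holds for clustering by institution. Children are recruited through institutions, reported age follows institution type, and the stated analysis makes no allowance for either. If it is followed as written and the ICC is above zero, intervals for prevalence and for contrasts between the three age bands are too narrow.

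Over the assumed range the understatement of width runs from a factor of 1.01 to about 2.4. In the middle case of 40 institutions and an ICC of 0.01 to 0.02 it is about 1.2 to 1.4. These figures rest on assumed numbers of equal-sized institutions and assumed ICCs, for which the article offers no basis. Unequal sizes would raise the design effect.

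Point estimates and the stated expected counts need not change, and an unseen analysis plan may already cover this. It should be corrected before analysis, but it is not a must-fix.

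**What to change.** - Compute prevalence and age contrasts with institution as the cluster: survey-design or cluster-robust intervals, GEE, or a mixed model with an institution effect. If there are few institutions or few positives, use a small-sample correction, because cluster-robust variances are themselves unreliable there.
- State what the prevalence is adjusted for, and carry the clustered variance through that adjustment, for instance by resampling institutions.
- Report the number of institutions, the number of children in each, and the estimated design effect.
- Analyse change between T1, T2 and T3 with paired methods or a model with child and institution effects. The reason is validity and efficiency: pairing would usually narrow these intervals.

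No new data should be needed, since institution must be known for the promised report of infections per institution. Results states that analysis follows data collection, so the change was still feasible when the article was written. The cost is a modest amount of modelling work and wider intervals for prevalence and age contrasts.

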## Results

The first study participant was enrolled in July 2020, and recruitment and enrollment continued until July 2021. We have recruited and enrolled 1850 children, 560 adults for the comparator group, and 83 adults for the validation group. We have collected samples from the children and the adults for the comparator group at the three time points (T1-T3). We followed up with participants in the adult validation group every 2 months and, as of the writing of this paper, we were at time point 7. We will conduct data analysis after the data collection period.

An amendment to the protocol was submitted to, and approved by, the Ethics Committee of the Tübingen University Hospital for blood collection from antibody-positive children during data collection at T3. This study is expected to conclude in November 2021.

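### The planned prevalence adjustment describes no allowance for sampling error in the assay's sensitivity and specificity; if both are entered as fixed, intervals at low prevalence can cover well below 95%

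*Protocol article*

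**What the plan says.** Data Analyses, in the protocol article's Methods, states: "The estimated prevalence will be computed and adjusted using the R package epiR (version 0.9-43"). No function, sensitivity, specificity or interval method is given.

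Four other places bear on this:

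- **Study Population** sets the size of the validation group: "For the adult validation group (n=40), the following individuals can participate in the study". Entry requires a previous SARS-CoV-2 infection, confirmed by PCR or ELISA.
- **Results** reports "83 adults for the validation group" as enrolled.
- **Laboratory Analysis** describes the saliva ELISA as already established and validated, by citation.
- **Sample Size** takes a confirmed-case rate of "567 out of 100,000 inhabitants", adds that "the number of unreported and asymptomatic infections is believed to be higher", and concludes "we expect to find at least 10.4 positive cases in children at T1".

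Prevalence of antibodies is the first stated objective. The Discussion promises results by age cohort and time point, and Study Design adds an adult profile.

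**The concern.** Saliva antibodies are a surrogate for past infection, so the natural reading of the adjustment is correction for test error. The usual correction (Rogan-Gladen) needs a sensitivity and a specificity. Both are estimates from finite samples. In its standard form the correction takes them as given and only rescales the binomial limits of the crude positive rate. The resulting interval reflects the survey's sampling error and nothing else.

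This matters most when infection is rare. A specificity of 0.99 gives about 18 false positives among 1850 children, more than the ten or so true cases expected at the confirmed-case rate. A small error in specificity then moves the estimate by more than the survey's own sampling error. Comparisons between age bands, waves, and children and adults would be read from intervals that look more precise than they are. The point estimate can also be zero or negative.

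**Working it through.** **1. The article's own figures.** Expected cases are N × 567/100,000.
- Children: 1850 × 0.00567 = 10.49 (stated 10.4).
- Adult comparators: 400 × 0.00567 = 2.27 (stated 2.2).

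Both reproduce, apparently truncated.

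**2. Inputs.** From the article: N = 1850, prevalence P = 0.00567 as a floor, 40 planned and 83 enrolled validation adults. Assumed, because the article does not give them: sensitivity Se = 0.85, specificity Sp, and the number m of negatives behind Sp. The last two are varied.

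**3. Formula.** With apparent rate p = Se·P + (1 − Sp)(1 − P), the adjusted estimate is (p + Sp − 1)/(Se + Sp − 1). Leaving out the common factor 1/(Se + Sp − 1), its variance has three parts:
- survey: p(1 − p)/N
- specificity: (1 − P)² Sp(1 − Sp)/m
- sensitivity: P² Se(1 − Se)/83

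An interval with fixed inputs keeps only the first.

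**4. Hand check at Sp = 0.99, m = 100.**
- p = 0.85 × 0.00567 + 0.01 × 0.99433 = 0.01476
- Survey SE = √(0.01476 × 0.98524/1850) = 0.00280
- Specificity SE = 0.99433 × √(0.99 × 0.01/100) = 0.00989
- Sensitivity SE = 0.00567 × √(0.85 × 0.15/83) = 0.00022
- True SE / survey SE = √(0.00280² + 0.00989² + 0.00022²)/0.00280 ≈ 3.67
- Approximate coverage = 2Φ(1.96/3.67) − 1 ≈ 41%

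The specificity part dominates and the sensitivity part is negligible.

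**5. Simulation.** 40,000 replicates per row. Survey positives, validation positives (83 adults) and validation negatives are drawn as binomials. Clopper-Pearson limits are adjusted with the estimated Se and Sp treated as known, then truncated to [0, 1].

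| Sp (negatives) | Coverage, P = 0.567% | Estimate ≤ 0, P = 0.567% | Coverage, P = 2% | Coverage, P = 5% |
|---|---|---|---|---|
| 0.99 (100) | 39% | 27% | 49% | 66% |
| 0.99 (300) | 62% | 22% | 73% | 82% |
| 0.995 (500) | 77% | 11% | 86% | 90% |
| 0.995 (1000) | 86% | 7% | 91% | 92% |
| 0.998 (1000) | 91% | 2% | 93% | 93% |
| 0.999 (2000) | 95% | 0.3% | 95% | 94% |
| 1 (known) | 96% | 0% | 95% | 94% |

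A separate run with Se = 0.90 gives the same picture at the floor: 39%, 73% and 94% for Sp 0.99 from 100, 500 and 5000 negatives, and 97% throughout for Sp = 1.

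**6. Sensitivity alone.** With specificity known exactly, coverage at 0.567% is about 96% with either 40 or 83 adults. At an assumed 10% prevalence it is 87% with 40 and about 92% with 83.

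**7. With propagation.** A Lang-Reiczigel interval covers 96-99.5% at 0.567% across the six estimated-specificity rows. A version based on beta draws (Se = 0.90, Sp 0.98-0.999, 100-1000 negatives) covers 93-97%.

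**The case against.** The strongest reply is that the article never says the inputs are fixed. It names a package, not a function, and naming a package does not rule out propagating the error elsewhere in R. A reader might infer that the named tool necessarily treats sensitivity and specificity as constants. The documents do not show that, and the package's behaviour was not checked here. Nor does the article state a 95% interval or label any outcome primary. Interval methods are often left to an analysis plan, and none is shown. All of this stands, and it makes the finding conditional.

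It is also fair that 0.567% is a confirmed-case rate which the article itself treats as a minimum. Calling it the planned prevalence, or saying that coverage will be far below 95%, goes too far. With specificity essentially 1, or resting on thousands of negatives, coverage at the floor is about nominal. The article does not place the assay anywhere in the range examined. A reader might also blame the small validation group. At the floor its size hardly matters, because the loss comes from specificity.

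What survives is narrower. The article commits to this adjustment down to the package version and describes no propagation of error. Its own validation cohort contains nobody who could inform specificity. The loss is reduced at 2-5% prevalence but does not disappear.

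**Conclusion.** The point holds as a conditional weakness, not a demonstrated error. If sensitivity and specificity are entered as fixed values, nominal 95% intervals for 1850 children can cover anywhere from about 39% to about 95% at the confirmed-case floor. The result depends on the specificity and on how many negatives support it. At 5% prevalence the corresponding range is about 66% to 94%. Sensitivity error becomes material only at higher prevalence, for example 87-92% coverage at an assumed 10%.

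These figures rest on an assumed sensitivity of 0.85, assumed specificities and numbers of negatives, independent sampling, and reading the adjustment as a correction for test error. Confidence is moderate. The change is worth making because prevalence is the first objective and Results places the analysis after data collection.

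**What to change.** Amend Data Analyses to say that prevalence for each wave, each age band and the adult group is adjusted for test error with an interval that propagates sampling error in both sensitivity and specificity. Suitable choices are the Lang-Reiczigel interval, or a Bayesian model with binomial likelihoods for the validation positives, the validation negatives and the survey, with prevalence bounded at 0. Report the numerators and denominators behind both inputs, including the source of the negatives. The named package may stay for the crude rate.

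The cost is one sentence and a few lines of R, with no new data. The intervals will be wider and look less favourable. If propagation was already intended, the sentence simply records it.

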### Ethics Approval and Consent to Participate

This study was conducted with the approval from, and consent form signed by, the parents and participants, according to the protocol that was reviewed and accepted by the Ethics Committee of the University Hospital Tübingen on June 24, 2020 (reference No. 20-231/BO1). Each study participant was protected against invasion of privacy. Written informed consent was obtained from the participants, with parental consent and participant assent from those 12 years of age and older. The trial was retrospectively registered at ClinicalTrials.gov (NCT04581889) on October 10, 2020.

